### Participants

Children aged between 7 and 15 years with CP will be invited to participate. Through the Cerebral Palsy Register of Norway (CPRN) we have identified 70 children with unilateral CP and 45 children with bilateral CP born in these health regions. The children must be able to use a personal computer mouse and they will be included if they understand the instructions and the intention of the computer game, regardless of IQ. Children with Gross Motor Function Classification System (GMFCS) level V (most severe CP)
[1] or who have severe visual or hearing impairments, or photosensitive epilepsy will be excluded. Participants will be recruited from the following counties: Nord- and Sør-Trøndelag (Health region Mid-Norway), Vestfold, Telemark, Aust- and Vest-Agder (Health region Southeast Norway) and from Rogaland (Health region West Norway).

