### Statistical methods

Data will be analysed using the IBM SPSS statistics software for Windows, version 19 (IBM Corp. Released 2010. IBM SPSS Statistics for Windows, Version 19.0. Armonk, NY: IBM Corp, USA) (Illinois, United States). Differences in group means for variables with a normal distribution will be compared with the Student’s *t-*test. Outcome measures not normally distributed will be analyzed using the Mann-Whitney *U* test. The Wilcoxon signed-rank test for two related samples will be used to compare scores at the two time points (baseline versus immediately after training). A univariate general linear model will be used to compute mean values for the neuropsychological tests and questionnaires adjusted for gender and SES, with the group as the fixed factor and sex and the SES as covariates. A full data analysis plan will be drafted before unmasking group adherence.

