### Estimation of sample size

The aim of the present study is to demonstrate a clinically significant effect of the training on working memory, and we defined this as a 10% score increase on the main outcome measure, the spatial span from the WMS-III, in those children who had performed the training as compared with those in the control group. In order to estimate the sample size needed to meet this aim, we applied results (mean and SD) from one of our previous intervention studies in adolescents born with extremely low birth weights (ELBW; birth weight (BW) of less than 1000 g), of whom two participants had CP (Løhaugen *et al.*[18]). Using these figures, we estimated (sample power 3) that we would need to recruit 100 participants in order to show a 10% improvement in spatial span following training, with an 80% power and a two-tailed alpha of 0.05. In order to allow for a dropout rate of 15%, we decided to include 115 participants.

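### The planned group comparisons do not adjust for baseline spatial span, which is measured before randomisation; the cost is precision and protection against chance imbalance, not validity

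*Protocol article*

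**What the plan says.** The Statistical methods section of the protocol article lists these analyses:

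- Student's t-test for group means of normally distributed variables.
- For the rest: "Outcome measures not normally distributed will be analyzed using the Mann-Whitney" *U* test.
- A Wilcoxon signed-rank test of baseline against post-training scores. This is a within-child comparison.
- A univariate general linear model giving adjusted means for the tests and questionnaires, "with the group as the fixed factor and sex and the SES as covariates".

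The section closes by promising a full analysis plan before group membership is unmasked.

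Table 1 schedules the spatial span board, the primary outcome, at all four visits including T1. The section on the baseline assessment places randomisation after that assessment. Under Participants the age range is wide ("Children aged between 7 and 15 years with CP will be invited to participate") and entry does not depend on IQ. The article describes no stratification or matching on baseline score.

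**The concern.** A child's own span score before training is an obvious candidate predictor of the score after training, and it will be on file for every randomised child. The only stated use of baseline scores is the Wilcoxon test, which gives no contrast between randomised groups. The one model that adjusts for anything adjusts for sex and SES.

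Two things are at stake. First, variation between children that baseline span could explain stays in the error term. Second, if the groups differ at baseline by chance, an analysis of follow-up scores has nothing to correct for it. The number of children is also close to fixed: the article identifies 70 + 45 = 115 eligible children in the register, exactly the recruitment target, so there is no reserve from which to recover lost precision.

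**Working it through.** **Inputs from the article (Estimation of sample size).** Design: "with an 80% power and a two-tailed alpha of 0.05". Target: "we defined this as a 10% score increase on the main outcome measure, the spatial span from the WMS-III". Source of the mean and SD: "we applied results (mean and SD) from one of our previous intervention studies"; neither value is printed. Result: "we would need to recruit 100 participants in order to show a 10% improvement in spatial span following training". Then: "In order to allow for a dropout rate of 15%, we decided to include 115 participants".

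**Assumptions.** 1:1 allocation. The baseline-follow-up correlation r is not given; 0.3, 0.5 and 0.7 are used. SDs are equal at the two visits.

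**1. The plan's own figure.** N = 100 cannot be reproduced directly without the mean and SD, so it is inverted. With 50 per arm, 80% power and two-sided 0.05:
- normal approximation: d = (1.960 + 0.842) × √(2/50) = 0.560
- noncentral t: d = 0.566

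A 10% difference at d = 0.566 implies SD/mean = 0.10/0.566 = 17.7%. N = 100 is therefore consistent with an unadjusted two-sample comparison at d = 0.566.

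**2. Completers.** 115 × 0.85 = 97.75, taken as 98, or 49 per arm. Unadjusted power at d = 0.566 is 79%.

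**3. Adding baseline span (ANCOVA).** The residual SD is SD × √(1 − r²), so the effective d is 0.566/√(1 − r²). The noncentral t is used with 95 degrees of freedom.

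**4. Change scores.** The SD of change is SD × √(2(1 − r)), so the effective d is 0.566/√(2(1 − r)), with 96 degrees of freedom.

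| r | d, ANCOVA | Power, ANCOVA | d, change | Power, change | Power, follow-up only |
|---|---|---|---|---|---|
| 0.3 | 0.593 | 83% | 0.478 | 65% | 79% |
| 0.5 | 0.653 | 89% | 0.566 | 79% | 79% |
| 0.7 | 0.792 | 97% | 0.731 | 95% | 79% |

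**5. Chance imbalance.** The SE of the baseline difference is √(2/49) = 0.20 SD. Given an imbalance of that size, the expected shift in the unadjusted follow-up difference is r × 0.20:
- r = 0.5: 0.10 SD, or 0.10/0.566 = 18% of the design effect
- r = 0.7: 0.14 SD, or 0.14/0.566 = 25%

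**6. Sensitivity to the SD that was borrowed.** Steps 3 to 5 read d = 0.566 as standardised by the raw follow-up SD. If the earlier study's SD was an SD of change, the change-score test has 79% power at 98 completers whatever r is. ANCOVA's d is then 0.566 × √(2(1 − r))/√(1 − r²), which gives 89% at r = 0.5 and 85% at r = 0.7. The gain is smaller at high r but does not vanish.

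**The case against.** **A later plan is promised.** The article condenses its methods, labels no analysis as primary, and defers detail to a plan that is not shown. Had it been silent on covariates, that would end the matter. It is not silent: it names an adjustment set, and baseline span is not in it. The promised plan is where to make the change, but nothing in the article signals that it will be made.

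**The linear model may not be the primary analysis.** The sentence covers all tests and questionnaires, and the study also has baseline-only aims (cognitive profiles by subtype) for which baseline adjustment has no meaning. This stands as a caution: reading the model as the efficacy analysis is an inference. It does not rescue the plan, because the alternatives, the t-test and Mann-Whitney test, carry no covariates at all.

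**Change scores may be intended.** The sample size section speaks of an increase and an improvement, which fits change scores, and the Statistical methods section does not settle it. So it cannot be said that baseline is certainly unused. At r = 0.7 the advantage of ANCOVA over change is then only 97% against 95%.

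**Stronger readings the text does not support.** A reader might infer that the unadjusted test is biased or has inflated type I error; averaged over randomisations it is neither. A reader might infer that a baseline difference carries over in full; only the fraction r does. A reader might rank age equally with baseline span; the documents give no evidence for that, and age may add little once baseline span is in the model. A reader might also object to choosing between the t-test and the Mann-Whitney test. The article does not say how normality will be judged, no harm from the choice has been quantified, and it is a separate matter from covariates.

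**Conclusion.** The point holds as one of efficiency. The stated group comparisons leave baseline spatial span out of the adjustment, although it is collected before randomisation. With 98 completers and d = 0.566 on the raw follow-up SD, adding it would raise power from 79% to 83%, 89% or 97% at r = 0.3, 0.5 or 0.7. Against a change-score analysis the gain is 18, 10 and about 2 percentage points (83 − 65, 89 − 79, 97 − 95).

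The direction holds for any clearly non-zero r. The size does not come from the documents: it rests on an assumed r, a back-calculated d, and an assumption about which SD the sponsor borrowed. The upper end should not be quoted as an expected gain. Confidence is high that adjustment is missing from the stated model, and moderate on how much it would be worth.

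**What to change.** Before unmasking, state in the analysis plan that the primary analysis is a linear model of t2 spatial span (when the waiting group is still untrained) on randomised group and baseline spatial span. Keep sex and SES; age is an optional further covariate. Report the adjusted mean difference with its 95% confidence interval.

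Use the same form, with each outcome's own baseline, for other tests and questionnaires measured both at T1 and at follow-up. If residuals are skewed, keep the model and give robust or bootstrap confidence intervals.

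The cost is plan wording and one or two degrees of freedom. No new data are needed.

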### Estimation of sample size

The aim of the present study is to demonstrate a clinically significant effect of the training on working memory, and we defined this as a 10% score increase on the main outcome measure, the spatial span from the WMS-III, in those children who had performed the training as compared with those in the control group. In order to estimate the sample size needed to meet this aim, we applied results (mean and SD) from one of our previous intervention studies in adolescents born with extremely low birth weights (ELBW; birth weight (BW) of less than 1000 g), of whom two participants had CP (Løhaugen *et al.*[18]). Using these figures, we estimated (sample power 3) that we would need to recruit 100 participants in order to show a 10% improvement in spatial span following training, with an 80% power and a two-tailed alpha of 0.05. In order to allow for a dropout rate of 15%, we decided to include 115 participants.

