### Neuropsychological assessment at baseline (t1)

The examination at baseline will include a full WISC- IV. Age-appropriate norms from the Scandinavian standardization will be used to calculate IQ scores. The comprehensive ‘Developmental Neuropsychological Assessment’ (NEPSY) will be applied to study memory and learning, language, attention and executive functions. At baseline the assessment lasts for approximately 3.5 hours including breaks. After completion of the baseline assessment, participants will be randomized to either training or treatment-as-usual.

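### Minor arithmetic slip: 115 enrolled covers 13% dropout, not the stated 15% (118 needed); separately, 115 equals the register count, with no stated margin for refusal or ineligibility

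*Protocol article*

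**What the plan says.** In the protocol article, Estimation of sample size, the target effect is relative: "we defined this as a 10% score increase on the main outcome measure, the spatial span from the WMS-III". The planning values come from another population ("we applied results (mean and SD) from one of our previous intervention studies in adolescents born with extremely low birth weights"), and the article does not print them. The result is that "we would need to recruit 100 participants in order to show a 10% improvement in spatial span following training". The power behind that number is 80%, at a two-sided significance level of 5%. The next sentence adds the allowance for loss: "In order to allow for a dropout rate of 15%, we decided to include 115 participants".

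Under Participants, the authors report that from the Cerebral Palsy Register of Norway "we have identified 70 children with unilateral CP and 45 children with bilateral CP", which makes 115. The same section lists the mouse-use and comprehension requirements and the exclusions (GMFCS level V, severe visual or hearing impairment, photosensitive epilepsy). Ethical perspectives says that families had agreed to be registered and to receive study information, and that the trial consent forms are still to come back. On allocation, the baseline assessment section says only that "participants will be randomized to either training or treatment-as-usual"; no ratio is given.

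**The concern.** There are two separate matters.

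- **Inflation for dropout.** A loss of 15% applies to those enrolled, so the required number must be divided by 0.85. Adding 15% to the required number gives too small a total. The article therefore pairs a dropout rate with an enrolment figure that does not preserve the 100 it says it needs.
- **Target and register count.** The enrolment target is the same number as the children identified before trial consent. The 15% covers loss after inclusion. Nothing in the article covers families who decline or children who prove ineligible.

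What is at stake is how the trial's sensitivity is described. If fewer than 115 are enrolled, the 80% figure would no longer describe the trial, and a null result should not be read against it.

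**Working it through.** **Inputs.** Required total 100, power 80%, two-sided alpha 0.05, dropout 15%, enrolment 115 (all from Estimation of sample size); register count 70 + 45 = 115 (Participants). Assumed: 1:1 allocation. The base figure of 100 cannot be rebuilt, because neither the mean and SD nor an absolute difference is printed, so it is taken as given.

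**Step 1: reproduce the plan's figure.** 100 × 1.15 = 115, an exact match.

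**Step 2: correct inflation.** 100/(1 − 0.15) = 117.6, rounded up to 118, which is 3 more than stated.

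**Step 3: what 115 delivers.** 115 × 0.85 = 97.75 completers. The largest dropout that still leaves 100 is 1 − 100/115 = 13.0%.

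**Step 4: power at the reduced size.** The standardised effect implied by 50 per arm is d = (1.960 + 0.842) × √(2/50) = 0.560. For a total of N completers, power = Φ(d × √(N/4) − 1.960). At N = 97.75, d × √(97.75/4) = 2.770, and Φ(2.770 − 1.960) = Φ(0.810) = 79.1%. At N = 98 it is 79.2%, and at N = 97, 78.8%. A noncentral t calculation (d = 0.566) gives the same three figures.

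**Step 5: detectable gain.** With 80% power held fixed, the detectable difference scales with √(100/N). At 97.75 completers it is 10% × √(100/97.75) = 10.1%.

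**Step 6: uptake scenarios.** The article gives no uptake rate, so the uptake column is assumed. Completers = 115 × uptake × 0.85.

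| Assumed uptake of 115 | Enrolled | Completers at 15% dropout | Power | Detectable gain at 80% power |
|---|---|---|---|---|
| 100% | 115 | 97.75 | 79.1% | 10.1% |
| 95% | 109.25 | 92.9 | 77.0% | 10.4% |
| 90% | 103.5 | 88.0 | 74.8% | 10.7% |
| 80% | 92 | 78.2 | 69.8% | 11.3% |

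**Step 7: what baseline adjustment could return.** Table 1 has spatial span measured at T1. Adjusting for it multiplies the residual variance by about 1 − r², where r is the correlation between baseline and outcome. Precision equal to that of 100 unadjusted completers needs 1 − r² = N/100. At 78.2 completers, r = √(1 − 0.782) = 0.47. At 97.75, r = √(1 − 0.9775) = 0.15. The article gives no value for r.

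**The case against.** The case against making much of this is strong, and most of it stands.

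- **The slip is small.** Three children and less than one power point separate the stated figure from the correct one. A reader might infer that the trial therefore fails to deliver its 80% power. The arithmetic does not support that: at the stated dropout, power is about 79%. If 100 was itself rounded up, which the article neither shows nor rules out, 97 to 98 could be enough.
- **Refusal and ineligibility come before inclusion.** They bear on whether 115 is reached, not on the power of 115 enrolled children. This stands, and it is why the register count is a recruitment matter.
- **The 115 may not be the raw or the only pool.** A reader might infer that the target requires every identified child to be eligible and to consent. Participants does not say whether the count was taken before or after the exclusions. It covers only unilateral and bilateral CP, which Objectives calls the two most common subtypes, while eligibility is CP in general. Trial status has recruitment running from August 2013 to June 2015, so children may age into or out of the range. The inference is therefore not secured.
- **The lower powers rest on assumed uptake.** A reader might take 70% as the trial's real power. No participation rate is given, so that figure is only a scenario.

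Two points survive. The stated pair of 15% and 115 does not agree with the required 100, whatever the uptake. And even if all 115 had been prescreened, Ethical perspectives shows that consent to this trial was still outstanding.

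**Conclusion.** The point holds as a minor arithmetic error with a separate feasibility remark. Taking the article's own 100 as correct, 15% dropout needs 118 enrolled; 115 leaves 97 to 98 children and about 79% power, and keeps 100 only up to 13% dropout. The power figure assumes 1:1 allocation and a two-sample comparison of means.

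The equality of the target and the register count (70 + 45) is a fact of the article, and no margin for refusal or ineligibility is stated. The size of that risk is unknown. If the 115 were the only source of participants, 5% non-participation with 15% dropout would bring power to about 77%, but the documents do not establish either condition.

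Nor can it be said that baseline adjustment makes good the loss. The general linear model under Statistical methods adjusts for sex and SES only, and the gain from adding baseline spatial span depends on an unstated correlation.

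**What to change.** 1. In Estimation of sample size, replace the dropout sentence with one of two equivalent statements: 115 enrolled allows for 13% dropout at 80% power, or 115 enrolled gives about 79% power at 15% dropout. State the allocation ratio on which this rests.
2. Say whether the 115 register children were counted before or after the exclusions, and whether other children may be recruited. Add power and detectable difference for a range of uptake, labelled as assumed; the table in the working can serve.
3. Consider adding baseline spatial span to the sex and SES model before group membership is unmasked, which is when the article says its full analysis plan will be drafted. Describe the gain as possible, not assured: about r = 0.47 would be needed for 78 completers to match 100.

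The cost is a few sentences, a small table and one covariate that is already collected. The stated power becomes slightly less favourable. No extra enrolment is requested.

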### Ethical perspectives

The Regional Committee for Medical Research Ethics (Norwegian Health Region II) approved the study protocol (project number: 2012/298). All invited participants consented to be registered and to receive information about relevant research studies through The Cerebral Palsy Register of Norway (CPRN). Information including consent forms was sent to the families by mail from the CPRN. The consent forms are to be returned to the CPRN to be transferred to the principal investigator of the research study. The families will then be contacted to schedule an appointment for baseline assessment. If the cognitive and neuropsychological testing indicates learning disorders, the child will be offered a referral to appropriate institutions to receive further assessment and diagnostic evaluation. All parents will be offered a meeting with the neuropsychologist to discuss the child’s results if wanted, as well as written reports. The CONSORT statement and the CONSORT statement for non-pharmacological interventions will be followed in the reporting of results
[50,51].

### Dissemination plan

The following publications are planned:

Based on results from examinations before training:

Paper 1: Cognitive profile (IQ) in Norwegian children with CP born preterm or at term.

Paper 2: Neuropsychological function in Norwegian children with cerebral palsy.

Based on results from after the training of working memory:

Paper 3: Short- and longterm effects on cognitive function of a computer-based working memory training program in children with CP.

Paper 4: Effects of a computer-based working memory training program on activities of daily living and psychological wellbeing in children with CP.

Based on results from examinations before training: Paper 1: Cognitive profile (IQ) in Norwegian children with CP born preterm or at term. Paper 2: Neuropsychological function in Norwegian children with cerebral palsy. Based on results from after the training of working memory: Paper 3: Short- and longterm effects on cognitive function of a computer-based working memory training program in children with CP. Paper 4: Effects of a computer-based working memory training program on activities of daily living and psychological wellbeing in children with CP.

## Discussion

It has been reported that the majority of children (80%) with a working memory capacity below the 10th percentile experience major problems in reading and writing as well as in mathematics
[43]. In children with CP, reduced working memory capacity is prevalent
[36], and has been shown to be related to deficits in arithmetic performance
[52]. A study by one of the researchers behind the present proposal described reduced working memory in children with learning difficulties related to reading
[53]. Other studies have found working memory to be relatively independent of a child’s general level of intelligence
[54], and to be a better predictor of academic success than IQ
[55]. Thus, taken together, all these studies suggest that improving working memory is likely to have a number of general positive effects on other cognitive functions, academic performance and behaviour. We therefore want to examine whether this also is true for children with CP.

The intervention method tested here has components that make it user friendly and cost-effective regarding time and economic resources in that it is computer-based, performed at home and has a relative short duration of intervention. If this kind of cognitive training proves to be effective in children with CP, we have provided important information and knowledge in the further development of cognitive intervention methods that may be applied within the child rehabilitation system.

Children with CP are often in need of multidisciplinary rehabilitation and special education interventions. There is a lack of evidence-based knowledge regarding cognitive function and effects of intervention methods in this patient group. In addition, assessing a comprehensive cognitive profile in children with CP will provide a better knowledge base for the planning of treatment and rehabilitation. To avoid ineffective and unnecessary treatment at high costs more scientific studies are needed. Improving working memory may have positive consequences at both an individual and family level, reduce the need for special education and improve social and daily-life functioning. The proposed study will enable recommendations regarding the effect of cognitive training in children with CP.

